###### Determination of Costs

Costs will include the costs of the intervention itself derived from the intervention as outlined in greater detail below as well as estimated costs of future hospitalizations and induced costs related to the intervention. Members of the UCT Health Economics Unit will be encouraged to participate in the collection of the input costs for the model. They have been working to cost out various items of care at the Vanguard clinical site along with members of the UCT Department of Medicine on a project for management where [name] is serving as an advisor and we will aim to collaborate and extend some of that work for this project.

Based on similar economic evaluations, the major costs of the intervention (excluding the research components) include the following:

1. Design and Development costs: these include primarily labour costs spent by quality improvement and clinical personnel finalizing the guideline protocols. These costs will have to be amortized over the life of the presumed intervention.
2. Implementation and Education Costs: these include training time for the managers and nurses to learn to use guidelines and risk tools, as well as training of clinical and office personnel who interact with case management personnel. These costs will need to be amortized over the course of the likely retention period of the individual practitioner.
3. Clinical Operating Costs: these include the ongoing costs to conduct the intervention, including time of the manager, as well as overhead and supply costs.
4. Information Technology Support Costs: these include ongoing support services such as data monitoring and backup, network support services, updates, and modifications.
5. Patient Utilization Costs: these include increases in testing, medication use, visits, and referrals that result from the intervention, calculated directly from the results of the intervention (i.e., change in utilization in the intervention arm compared with the change in the usual care arm). These may be offset by efficiencies gained by transferring some patient care activities from physicians to lower cost personnel such as a nurse practitioner.
6. Direct non health care costs including transportation to the clinic, assistance from caretakers and the costs of the patient seeking care will be included if significant

**Determination of Effectiveness**

The model will determine patient benefits by quantifying the decrease in cardiac risk factors (e.g., LDL and blood pressure, and smoking rates) and increase in cardiac medication use (e.g., blood pressure medications, aspirin, ACE-Inhibitors to be consistent with the drug formularies) from the intervention and then estimating the benefits of these changes from the medical literature, including trials of medications and studies of risk factor modification. We will use studies of other multi-factorial interventions and observational modelling studies to determine whether the benefits of carrying out multiple prevention strategies results in an additive, less than additive, or synergistic changes in cardiac risk. Confidence intervals on the relative risks of these benefits will be reported for sensitivity analyses around the key parameters and for a probabilistic sensitivity analysis.

The model will assume that prevented cardiac events will be divided among cardiac death, coronary interventions (PTCA and CABG) and other hospitalizations for CAD in a distribution similar to that in current practice. Changes in quality of life will be taken from the literature on the utilities of different health states following non-fatal cardiac events. The model will then estimate the increase in quality-adjusted life-years (QALYs) generated by the intervention.

**Data Collection**

In each model the adult population will be defined according to age, sex, tobacco status, and BMI in the low cost strategy and age, sex, tobacco status, cholesterol, and diabetes status in the high cost screening strategy. Growing on the experience from evaluating the prevalence, distribution, and medications patterns of hypertension in South Africa, (Steyn *et al*, 2001) we will use the Demographic and Health Survey (DHS) of South Africa to determine the smoking rates, body mass index, and family history of CVD. Estimates on diabetes status and cholesterol levels will be pulled from smaller representative studies (Levitt *et al* 1993, 1999) or our new pilot data since this information was not collected in the DHS. We will use the Statistics South Africa’s database available in the public domain to determine the population by age deciles in South Africa. Utility weights will come from EQ-5D results from the above integrated care guideline as well as other local and international sources.

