The fieldworkers assessed anthropometric measurements, blood pressure, pulse rate, and peak expiratory flow rate on each participant at their home. Systolic and diastolic blood pressure and pulse measurements were taken 3 times with the patient seated and the left arm at the level of the heart after the participant was seated for 5 minutes. An Omron M1 electronic blood pressure manometer was used. In addition information on smoking status, diabetes status, medications for hypertension, and body-mass-index were collected and will be used in the calibration model. Population based means for these values with standard errors will be used to model death rates from CVD.

To assess calibration (the degree of similarity between observed and predicted risks) we will calculate the mean predicted risk of cardiovascular disease at 10 years and the observed risk at 5 years obtained using the 5 year Kaplan-Meier estimate. We then compared the ratio of the predicted to the observed cardiovascular disease risk for patients in the validation cohort in each tenth of predicted risk.

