We included the following risk factors in our analysis to compare a lab-based tool to a non-lab based tool, using the value closest to the entry date to the cohort for each patient: age (in single years); gender (men v women); smoking status (current smoker, non-smoker—including former smoker); systolic blood pressure (continuous); ratio of low density lipoprotein cholesterol to high density lipoprotein levels (continuous); body mass index (continuous); current prescription of at least one antihypertensive (yes or no), and diabetes status (yes or no). Having calibrated the model from the national data we can then apply this data from this specific validation cohort. We calculated the 5 year estimated cardiovascular disease risk for each patient in the validation dataset. For development and validation of the new risk score we will use Cox proportional hazards regression to assess the “lab-based” model and compare it with the “non lab-based” model.

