## Research procedures and data collection

Participants who are eligible and provide consent for the validation study will be asked a few questions to establish smoking status, treatment for hypertension and diagnosis of diabetes, and will undergo the following measurements: blood pressure, height, weight, hip and waist circumference. Blood pressure will be taken using an electronic device, and will follow the American Heart Association protocol, where multiple measurements (three) are taken over the period of the interview a minimum of two minutes apart. The average of these readings will be used (Pickering 2005). Participants in the validation study will also undergo venesection and blood will be drawn for triglycerides and HDLC/LDLC ratio. Trial participants with diabetes requiring medication will undergo an HbA1C. Venesection will be performed by the usual nurses responsible for phlebotomy at the clinic, but bloods will be transported to and analysed by a private pathology service. The need for these exploratory assessments and analyses is illustrated by the finding that in community surveys in the target areas, the HDLC to TC ratio was found to be higher than in Caucasian populations (Mollentze 1995, Steyn 1989, Oelofse 1996). This suggests that TC levels will not serve as a satisfactory proxy measure for cardiovascular risk associated with apo B-related lipoprotein particles such as LDLC. We therefore propose to explore whether HDLC/LDLC ratios might serve as a better indicator of lipid-related risk for cardiovascular disease in this population.

Participants eligible for the trial will undergo a structured interview administered by a trained fieldworker. The same questionnaire will be applied irrespective of the target condition reported by the participant, as data collected are applicable across all cohorts.

Data collected will include:

- Patient contact details to facilitate administration of follow-up interviews
- Demographic data (date of birth, sex)
- National identity numbers to permit linkage with the national mortality register, which is estimated to record more than 90% of all deaths in South Africa (Statistics South Africa 2005)
- Hospitalisation folder numbers, if available, to permit linkage with hospitalisation databases
- Measurement of cardiovascular risk parameters (e.g. blood pressure, waist circumference)

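### The economic model's low-cost and high-cost screening strategies both leave out systolic blood pressure and antihypertensive use, and the low-cost one leaves out diabetes, so neither matches the tools being validated

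*Combined protocol and SAP*

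**What the plan says.** The two screening strategies are defined in one place only, the Data Collection paragraph of the Economic Evaluation Model. The model population is described by "age, sex, tobacco status, and BMI in the low cost strategy and age, sex, tobacco status, cholesterol, and diabetes status" in the high-cost strategy.

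The validation study uses a longer list. Risk Prediction Validation gives the factors for comparing the lab-based with the non-lab-based tool: age, gender and smoking, then "systolic blood pressure (continuous); ratio of low density lipoprotein cholesterol to high density lipoprotein levels (continuous); body mass index (continuous"), then "current prescription of at least one antihypertensive (yes or no), and diabetes status (yes or no"). Proposed Model Calibration Approach repeats the same list. For the 1998 Demographic and Health Survey (DHS), that section describes seated blood pressure readings and says that information on "smoking status, diabetes status, medications for hypertension, and body-mass-index were collected and will be used in the calibration model".

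Research procedures and data collection has validation participants asked about "smoking status, treatment for hypertension and diagnosis of diabetes, and will undergo the following measurements: blood pressure, height, weight", along with hip and waist circumference. The Background and Significance section of the validation study describes the non-lab model as needing history and physical examination only.

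**The concern.** One purpose of the economic model, in the Synopsis, is to compare screening strategies. The validation study's Background and Significance section adds that the simple tool's cost-effectiveness in South Africa will be assessed. The Costs paragraph prices screening visits and screening blood tests, so this is a live analysis.

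For it to inform policy, the strategies in the model have to be the tools that the validation study evaluates. If the low-cost strategy is a four-variable instrument, its cost-effectiveness says nothing about the tool that the Synopsis plans to place in later versions of the guideline. If diabetes status goes only to the high-cost strategy, a difference between the strategies cannot be put down to the laboratory test.

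**Working it through.** No power, sample size or error-rate figure is involved, and the plan gives no figure to reproduce. The check sets the variable lists side by side.

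| Risk factor | Lab v non-lab comparison (validation and calibration sections) | Low-cost strategy | High-cost strategy |
|---|---|---|---|
| Age | yes | yes | yes |
| Sex | yes | yes | yes |
| Smoking | yes | yes | yes |
| Systolic blood pressure | yes | **no** | **no** |
| Antihypertensive prescription | yes | **no** | **no** |
| Diabetes | yes | **no** | yes |
| BMI | yes (tool not stated) | yes | no |
| Lipids | LDL/HDL ratio | no | "cholesterol", type not stated |

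**Count for the low-cost strategy.** Eight listed factors less the lipid ratio leaves 8 − 1 = 7 that need no lipid test. The strategy has age, sex, smoking and BMI: 4 of 7. It lacks 7 − 4 = 3: systolic blood pressure, antihypertensive use and diabetes.

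**Count with BMI set aside.** The plan does not say which tool uses BMI. Without it, 7 − 1 = 6 factors remain. The low-cost strategy has 3 of the 6 and the high-cost strategy has 4 of the 6. Blood pressure and antihypertensive use are missing from both.

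**What separates the two strategies.** They differ on three items: BMI (low-cost only), cholesterol (high-cost only) and diabetes (high-cost only). For validation participants, the plan obtains diabetes by question and BMI by measurement. Of the three, only cholesterol requires a blood test, so the contrast is not that of the test alone.

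**Whether another section restores the missing items.** Blood pressure reaches the economic model by three other routes:

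- Calibration starts from transition probabilities based on the Framingham equations, which use blood pressure.
- Community Population takes a baseline risk profile from the clinics.
- Model Structure and Determination of Effectiveness use blood pressure changes as intervention effects.

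None of these adds blood pressure to what a screening strategy knows about a person. The Sensitivity Analysis paragraph varies input values, not the set of predictors that defines a strategy, so it would not expose the gap.

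**Source of diabetes data.** The Data Collection paragraph says that diabetes status and cholesterol were not collected in the DHS. Proposed Model Calibration Approach plans to use diabetes status from that same survey, both for calibration and for checking the WHO charts.

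**The case against.** The strongest reply is that the Data Collection paragraph describes a population and its data sources and is not a score specification. Overview also says that the end product is a set of model specifications, so these lists need not be final. That is a fair caution. It limits the finding to the text as written. But the paragraph labels the two lists as low-cost and high-cost strategies, and no other section defines them.

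A second reply is that the validation sections give one combined list and never assign factors to tools. BMI may be meant to replace lipids in the non-lab tool, in which case its absence from the high-cost list is intended. This stands. It rules out a demand that the strategies differ only in the lipid measure. It does not explain the loss of blood pressure and antihypertensive use from both lists, or of diabetes from the low-cost one.

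A reader might go further in three ways that the documents do not support:

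- *The comparison is biased towards laboratory screening.* Diabetes information favours the high-cost strategy, but that strategy also lacks BMI and bears the cost of the blood test. The net direction cannot be derived.
- *The whole model ignores blood pressure.* It does not, given the three routes above.
- *Family history of CVD has been added to a tool.* It is named as a survey input and appears in neither strategy's list.

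**Conclusion.** The concern holds for the screening-strategy analysis. As written, the low-cost strategy carries 4 of the 7 factors that need no lipid test. Both strategies lack systolic blood pressure and antihypertensive use, and diabetes status is given to one strategy only. The resulting comparison would not apply to the tool under validation, and it would mix the value of the blood test with that of diabetes information available by history. If the lists are exhaustive, two people of the same age, sex, smoking status and BMI, one with a systolic pressure of 120 mmHg and the other 180 mmHg, would share one risk cell in the low-cost strategy.

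This rests on two assumptions: that the lists are meant to be complete, and that the seven non-lipid factors are available to a tool based on history and examination. The second follows from how the plan describes the tool and from what it collects. The size and sign of the effect on the cost-effectiveness ratio cannot be computed from the documents. The Disease Model comparison of standard care with guideline-based case management does not use these lists and is unaffected, as are the trial's primary endpoints.

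**What to change.** In the Data Collection paragraph of the Economic Evaluation Model:

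1. Define each strategy by the predictors of the corresponding tool as validated. Put systolic blood pressure, antihypertensive use and diabetes by history in both.
2. State which of BMI and the LDL/HDL ratio belongs to each tool, here and in Risk Prediction Validation, and replace the unspecified cholesterol measure accordingly.
3. Take blood pressure and antihypertensive use from the 1998 DHS, which the calibration section says holds them.
4. Reconcile the source of diabetes status. One section says the DHS did not collect it, and another plans to use it from there. If the distinction is between reported and measured diabetes, say so.

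The cost is a rewording, two or three more model inputs, and more risk-factor cells to populate. Blood pressure and hypertension medication need no new data collection. Whether diabetes does depends on the answer to item 4.

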**Costs**

Resource use costs will include direct and non-direct health care costs, including informal caregiver time, and patient time, consistent with current recommendations for cost-effectiveness analyses. Direct health care costs primarily considered will be screening costs (e.g. clinic visits), costs of the medication, health care worker time, and costs of treating CVD events (both acutely and chronically). Direct non health care costs including transportation to the clinic, assistance from caretakers and the costs of the patient seeking care will be included if significant.

Screening costs will include the cost of the visits and the costs of the screening blood tests. The cost per visit will be according to the “scale of benefits” in South Africa. These are the levels that are reimbursed by third party payers and are considerably less than those recommended charges by the South African Medical Association (SAMA) and medication costs will be derived from local drug formulary information. Side effect costs and additional laboratory testing will be assessed. Treatment costs for the morbid sequelae of the risk factors—angina, myocardial infarction, sudden cardiac death, and cerebrovascular accident—are not directly itemized for each diagnosis in South Africa. Estimates from a bottom up approached used in the DCP2 analyses will be used.

**Sensitivity Analysis**

Univariate sensitivity analyses will be conducted on all input parameters including costs, prevalence estimates, and transition profanities, quality-of-life values, the relative risk reduction from treatment, and the discount rate. A probabilistic multivariate sensitivity analysis will then be performed with a Monte Carlo simulation of 1000 iterations.

## Recruitment and enrollment

Patient recruitment, enrolment and data collection will be conducted jointly for the validation study and trial. Patient inclusion and exclusion criteria differ between the validation study and trial, and have been described under the sections detailing the respective studies. Criteria are summarised in Table 3. We expect a large proportion of patients will qualify for both the validation study and trial. Others will be eligible for one of these studies, and some for neither.

**Table 3: Inclusion/ exclusion criteria for patients participating in validation study and trial**

| **Study** | **Validation study** | **Trial** |
| --- | --- | --- |
| Inclusion criteria | - Age ≥ 35 years *and* - Written consent to participate in the study | - Age ≥ 18 years *and* - Planning to reside in the area for the next year *and* - Written consent to participate in the study *and* - Self-reported diabetes on treatment *or* - Self-reported hypertension on treatment *or* - Self-reported asthma/ chronic bronchitis/ emphysema on treatment *or* - Cough/difficult breathing > 2 weeks (and not on treatment for tuberculosis in the past 3 months) *or* - The Center for Epidemiologic Studies Depression Scale (CES-D 10 Scale) score of 10 or more(Radloff 1977, Andresen 1994, Cheung 2007) |
| Exclusion criteria | - Prior cardiovascular event (e.g. stroke, myocardial infarct) - Acute and/or terminal condition precluding participation such as AIDS or cancer - Psychiatric diagnoses precluding participation such as schizophrenia, dementia and other cognitive impairment measured by self-reported or medical history. - Unavailable or no South African identity number | - Acute and/or terminal condition precluding participation such as AIDS or cancer - Psychiatric diagnoses precluding participation such as schizophrenia, dementia and other cognitive impairment measured by self-reported or medical history. |

Participants will be recruited at the 38 Eden and Overberg public sector community health centres (CHC) and clinics selected for inclusion in the trial. The majority of patients seeking care from these public sector clinics are poor and from the underserved sectors of the South African population. Of this group of possible study participants the majority will either be people of African descent (speaking predominantly IsiXhosa) or people of mixed race ancestry (speaking predominantly Afrikaans). Most people will also have some proficiency in English. Participants will be recruited from patients attending ambulatory outpatient services, and patients requiring emergency care, urgent referral or terminal care will be excluded.

Trained fieldworkers will be responsible for recruitment, enrolment and data collection procedures, under the supervision of the trial co-ordinator, a nursing sister with 20 years’ fieldwork experience in community and clinic-based surveys. In each clinic waiting room patients 18 years or older attending ambulatory services will be invited to be considered for participation in the study, and if willing, will be asked to meet a fieldworker after their consultation with the nurse or doctor and collection of medication from the dispensary. Trained fieldworkers will screen these patients using a structured questionnaire, and eligible patients will be invited to participate further and informed consent will be obtained. Screening and enrolment procedures are summarised in Figure 4.

**Figure 4: Overview of screening procedures and enrolment for validation study and trial**

##

## Research procedures and data collection

Participants who are eligible and provide consent for the validation study will be asked a few questions to establish smoking status, treatment for hypertension and diagnosis of diabetes, and will undergo the following measurements: blood pressure, height, weight, hip and waist circumference. Blood pressure will be taken using an electronic device, and will follow the American Heart Association protocol, where multiple measurements (three) are taken over the period of the interview a minimum of two minutes apart. The average of these readings will be used (Pickering 2005). Participants in the validation study will also undergo venesection and blood will be drawn for triglycerides and HDLC/LDLC ratio. Trial participants with diabetes requiring medication will undergo an HbA1C. Venesection will be performed by the usual nurses responsible for phlebotomy at the clinic, but bloods will be transported to and analysed by a private pathology service. The need for these exploratory assessments and analyses is illustrated by the finding that in community surveys in the target areas, the HDLC to TC ratio was found to be higher than in Caucasian populations (Mollentze 1995, Steyn 1989, Oelofse 1996). This suggests that TC levels will not serve as a satisfactory proxy measure for cardiovascular risk associated with apo B-related lipoprotein particles such as LDLC. We therefore propose to explore whether HDLC/LDLC ratios might serve as a better indicator of lipid-related risk for cardiovascular disease in this population.

Participants eligible for the trial will undergo a structured interview administered by a trained fieldworker. The same questionnaire will be applied irrespective of the target condition reported by the participant, as data collected are applicable across all cohorts.

Data collected will include:

- Patient contact details to facilitate administration of follow-up interviews
- Demographic data (date of birth, sex)
- National identity numbers to permit linkage with the national mortality register, which is estimated to record more than 90% of all deaths in South Africa (Statistics South Africa 2005)
- Hospitalisation folder numbers, if available, to permit linkage with hospitalisation databases
- Measurement of cardiovascular risk parameters (e.g. blood pressure, waist circumference)
- Processes of care received at the clinic: e.g. foot and eye examinations, counselling re weight loss and smoking cessation, referrals
- Medication received at the clinic (name, dose, duration)
- Dates prescriptions were filled at the clinic (to establish proportion covered by filled medication), as a proxy of adherence
- Health related quality of life (EuroQol 5D) to establish local utilities for a range of health states in those with chronic diseases for use in the economic model. The EuroQol has been widely used and validated in South Africa, and approved translations are available for the languages required for this study.
- Symptom severity: St Georges Respiratory Questionnaire (Jones 1991)
- Smoking history
- Health care utilisation (clinic visits, hospitalisations, use of private providers)
- Income and changes due to current illness
- WHO’s Disability Assessment Schedule II (Posl 2007)
- Expenditure on health care utilisation

The questionnaire is currently in development, and will be piloted prior to implementation in the trial. Once approved by the HREC it will be translated into Xhosa and Afrikaans in accordance with internationally accepted practices (Guillemin 1993). Certificates of translation will be submitted to the HREC.

Interviews will be conducted using computers, which we have previously used in similar field work data collection exercises in South Africa (Seebregts 2008). Based on previous experience with a similar questionnaire, interviews administered using such computers will last between 20 minutes and one hour, depending on the number of medications to be documented, and the extent of healthcare utilisation reported by the respondent.

Recruitment will occur during the month prior to the commencement of educational outreach and is estimated to last up to two weeks in each clinic. Patients will be re-interviewed once by appointment: approximately 12 months after the outreach training started (12 to 16 months after recruitment). Recruitment will start in March 2011and will be staggered across the 38 trial clinics .

The trial co-ordinator will recruit fieldworkers from local community networks, and preference will be given to those with experience in community based surveys. Excellent knowledge of the community will be a pre-requisite to help find participants who do not return to the clinic for follow-up interviews. Fieldworkers will undergo a three to five day training covering: enrolment procedures and consent, measurement of blood pressure and other parameters, use of the handheld computer and general clinic staff liaison and interviewing skills.

